### Blinding

Due to the nature of the intervention neither the patient-caregiver dyads nor the intervention nurses (for the face-to-face FOCUS+ intervention) can be blinded to allocation. Those conducting the data analyses will remain blind as to what trial arm dyads were randomized to until the end of the last data-collection point.

## Data collection, management, and analysis

### Data collection methods

The outcomes and outcome measures are described in 2.4. Quantitative data will be collected via computer-assisted self-interview in the presence of a data collector that can assist dyads with the completion of the questionnaires at T_0_ and T_1_. In case of tightened measures to contain the COVID-19 pandemic, data collection at T_0_ and T_1_ via a GDPR-approved online platform (e.g. MS Teams, Zoom,..) will be allowed, if necessary. The decision-making process is visualized in Fig. 3 and will be recorded for each dyad in each country. At T_2_, questionnaires will be self-administered online (without the presence and support of a data collector), with a telephone follow-up in case of nonresponse. The questionnaires were pilot tested among a small number of dyads before the start of the study to identify problems and limitations concerning respondent comprehension and acceptability.

**Fig. 3 Fig3:**
[figure not shown]
Decision-making process for data collection procedure in light of possible COVID-19 developments

To address the aim regarding the evaluation of the process of implementation both quantitative data and qualitative data will be collected throughout and after the interventions in each country and used for the evaluation:Detailed documentation of the recruitment process allows us to obtain information about the way patients and family caregivers were recruited and their reasons for participating or not.To measure the extent to which the intervention is implemented as intended (fidelity and consistency across the countries), the nurses delivering the intervention will be required to audio record intervention sessions, allowing members of the research team to complete a structured intervention checklist on a random sample of recordings every 3 months to record any deviations from the program. Adherence to the intervention is monitored by the use of these checklists.Repeated interviews with nurses who delivered the face-to-face FOCUS+ intervention in each country (*n* = 6 in total) and research staff supporting the delivery of the Web intervention (*n* = 6 in total) are also planned. These interviews will provide information on perceived barriers and facilitators to the delivery of the intervention and their experience or observations on the elements of the interventions that may represent mechanisms/agents of change. If necessary, in light of the COVID-19 pandemic, these interviews will take place online.A selection of 10 dyads who received either of the interventions is interviewed in every country to explore their perception of the intervention, their experience of the impact of the program, the core elements of the program that were central to their experience, and any recommendations for the further development of the intervention. The interviews will be conducted with a minimum of 10 dyads in each country, to include four dyads who complete either intervention and two dyads who did not complete either intervention. This information will allow consideration of the mechanism of impact or agents of change. All interviews will be audio-recorded and transcribed verbatim in the local language.

To reduce loss to follow-up and improve retention, retention gifts with the logo of the study on them will be provided after the completion of each data collection. These gifts are a coffee mug at T_0_, a magnetic notepad at T_1_, and plant seeds at T_2_. With these gifts, we intend to encourage participants to complete the data collections.

### Data management

The data collected through the questionnaires will be coded and stored in a safe data environment. Data cleaning will be carried out following a data cleaning protocol already developed and used by the coordinating partner Vrije Universiteit Brussel.

The consortium certifies that all research activities will adhere most strictly to all applicable legal, ethical, and safety provisions of the individual states and the EU. Participants will conform to relevant EU legislation including (1) The Charter of Fundamental Rights of the EU, December 2009 and (2) EU Regulation 2016/679 on the protection of natural persons concerning the processing of personal data and on the free movement of such data (GDPR).

The overall trial manager (Vrije Universiteit Brussel) will take the overall responsibility for data management throughout the DIAdIC project. Ultimately responsibilities for data management will be transferred to consortium partners to allow a collaborative and efficient collection of research findings throughout the time of the project. The Data Management Plan is added as a supplemental file.

### Statistical methods/data analysis

#### Quantitative analysis

Four main analyses will take place.Primary hypotheses testing*Testing the null hypothesis of the first primary endpoint: emotional functioning.*

The effectiveness of the FOCUS+ face-to-face intervention and the iFOCUS web-based intervention will be compared with the standard care (control group) for each participant population (patients/caregivers) separately. In total, 4 comparisons are performed for one outcome variable (alpha = 0.0125). The hypotheses related to the first primary outcome (emotional functioning) will be tested using a mixed model (per participant population) with the T1 measurement value for emotional functioning as the outcome variable, recruitment center as random effect and randomization group, and the baseline measure of emotional functioning (T0) as predictor variables. We will perform analyses on both ‘intention-to-treat’ and per-protocol principles. The primary principle is intention-to-treat. After completion of the baseline measurement (T0), dyads will be randomized to one of the trial arms. All randomized dyads will be included in the mixed model. Multiple imputations will be applied. Predictors for the imputation model will include the baseline measurement, randomization group, age, and other variables (e.g. severity of the illness). The secondary principle is the per-protocol analysis that functions as a sensitivity analysis. The per-protocol population will be defined as dyads who have completed all sessions of the FOCUS+ or iFOCUS intervention (except for dyads in the control group) and T1 measurement. By including the baseline measurement as a predictor variable (ANCOVA), preexisting differences will be controlled for, enhancing the sensitivity of the analyses. To interpret the magnitude of the effects for the different outcomes, we will estimate effect sizes (Cohen’s d).b.*Testing the null hypothesis of the second primary endpoint: self-efficacy (the Lewis´ Cancer self-efficacy scale from FOCUS)*

As per the fixed sequence (FS) procedure, the null hypotheses of the second primary endpoint (self-efficacy) will only be tested if a significant result is found for the first primary endpoint (emotional functioning). The same strategy is then followed for the analyses as for the first primary endpoint, with an alpha level of 0.0125.(2)Secondary hypotheses testing

All identified secondary endpoints (Quality of Life [including separate items of hopelessness, anxiety, depression], benefits of illness, coping, dyad communication, all at T1) will be evaluated by testing the FOCUS+ and iFOCUS against care as usual (control group) for each participant population (patients/caregivers) separately. In total, 4 comparisons are performed for each outcome variable. For each secondary outcome variable, a mixed model is applied with the T1 measurement value as the outcome variable, recruitment center as random effect, and randomization group and baseline measurement of the variable (T0) as predictor variables. We will perform analyses on both ‘intention-to-treat’ and per-protocol principles, applying the same principles as described above.

By including the baseline measurement as a predictor variable (ANCOVA), preexisting differences will be controlled, enhancing the sensitivity of the analyses. To interpret the magnitude of the effects for the different outcomes, we will estimate effect sizes (Cohen’s d). All statistical tests will be two-sided and considered significant if *p* < 0.0125.

All primary outcomes and secondary outcomes as listed above will also be analysed at T2 (6 months) to evaluate longer-term effects, using the same analysis procedures.

The cost-effectiveness of the interventions will be determined by analyzing patterns and costs of healthcare utilization and effects on quality of life. Costs will be estimated by combining the reported frequency of health care use by participants with country-specific unit costs for each service domain. Quality of life will be measured by combining EQ5D5L with country-specific preference weights. We will evaluate the robustness and consistency of results in population-specific outcome measures EORTC, FACT-G and CQOLC. Data will also be collected on the types and amounts of informal care provided to patients in each arm of the study, to investigate if the amount or patterns of informal care change as a result of the intervention. The outputs will be mean costs of care for patients in each arm of the study, cost per year of life gained (if survival is affected significantly by the intervention and the costs in the intervention groups overall are higher), and (if appropriate) the additional costs of achieving a better quality of life outcomes (including estimates of cost per quality-adjusted life-year gained).(3)Exploratory hypotheses testing

For all exploratory endpoints, two-sided statistical tests will be considered significant if *p* < 0.05.

For the outcomes that are measured identically for the patient and the caregiver, we will assess the effect on the dyad as a whole (i.e. both patient and family caregiver). For the outcome instruments that led to comparable estimated differences between FOCUS+ and standard care and iFOCUS and standard care, the effect will be assessed on the dyad as a whole by adding an extra level (dyad) to the linear regression model.For each of the primary and secondary endpoints, subgroup analyses will be performed using formal interaction tests to explore the extent to which the outcomes of the trial differ by country, gender, and socioeconomic status. Interaction terms between respectively country, gender, and socioeconomic status on the one hand and the trial arms on the other hand will be added to the analysis models. For the country variation multilevel mixed model analyses will also be performed to additionally account for potential clustering by country (i.e. participants nested within a country). Outcomes will be analysed with country as random factor.(4)Other analysesBackground reports describing care as usual for people with advanced cancer will facilitate the understanding of the results of the between-country comparisons.Process evaluation of the implementation of the interventions will be analyzed following the MRC framework for evaluating complex interventions [30], integrating normalization process theory (NPT) [31] and the RE-AIM framework [32]. Data analysis for the process evaluation will include a) standard statistical descriptions of the quantitative data from the intervention checklist and routine monitoring to describe adherence to the implementation. This analysis will determine cut-off points for good intervention adherence and, hence, inform the per-protocol analyses; b) analyses of the qualitative data (semi-structured interviews with patients and their family caregiver and post-intervention interviews with the nurses who delivered the face-to-face FOCUS+ intervention) will be performed (see below - Qualitative analysis).

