### Sample size calculation

We consider the demonstration of an intervention effect (for each of both interventions) on at least one of the primary endpoints for either the patient or the caregiver as a success. A pre-determined strict fixed sequence (FS) procedure defines the prospectively hierarchical ordering of the endpoints, for this study the hierarchical order is emotional functioning (1) and self-efficacy (2). Testing of null hypotheses proceeds according to their hierarchical order, that is, H(1)0 is tested first at a significance level of 5%, and if H*(*1*)*0 is rejected then H*(*2*)*0 is tested at the same significance level, otherwise H*(*2*)*0 is not tested at all. The strict FS approach has the highest power for testing the first hypothesis (outcome: emotional functioning) compared to the other methods, as it does not save any portion of alpha for testing later hypotheses [10]. The reference mean value for emotional functioning from EORTC for all cancer patients, stage III-IV is 71.5 (SD: 23.8) [28]. Alpha is set at 0.0125 instead of 0.05 to account for multiplicity (2 comparisons with control group * 2 participant groups [patients and caregivers]). We set 1-beta (i.e. statistical power) at 0.9. The expected difference between the control group and the intervention arms in the primary outcomes is 0.375 SD at T1 (12 weeks).

With these parameters *n* = 203 is needed in each arm across all countries (i.e. 609 in total). Anticipating a 65% retention rate at T1, which is more conservative than found in previous studies in the USA on the FOCUS interventions [5–7] due to the advanced cancer population included in this study, 938 dyads must be enrolled across the 6 countries (313 per group). This means that 156 dyads (i.e. 52 in each of the 3 arms) need to be enrolled in each country. Based on previous studies in the US [5–7] we expect an enrolment rate of 55% of those dyads referred to the study, meaning that about 282 dyads will need to be screened and identified in each country. The feasibility of recruitment has been evaluated based on previous research and discussions with clinicians in eligible hospitals.

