We anticipate some limitations and challenges in the DIAdIC trial. First, the inclusion of participants might be difficult for several reasons. As the target population includes patients with advanced cancer with a limited life expectancy of maximum 2 years and their family caregivers, eligible patient-caregiver dyads might be reluctant to enroll in a time-consuming trial. They might feel too tired or want to spend the time they have left doing different things. Additionally, a dyad can only participate in the trial when both the family caregiver and the patient agree to participate. Hence, we need consent from two people to include one participating entity or dyad in the study, which can cause the enrolment rate to be lower than other studies. Second, to address all the different outcomes of the DIAdIC trial, data will be collected three times from patient-caregiver dyads through long self-administered questionnaires, which may cause a considerable burden and can lead to high nonresponse. To limit the risk of nonresponse, the data collector is present at T_0_ and T_1_. For T_2_ the data collector will do a telephone follow-up in case of nonresponse. Third, the complexity of the study and the many aspects of tailoring and context does not allow for unambiguous identification of the active component of the interventions. This challenge is anticipated by conducting a thorough process evaluation to determine the mechanisms of action of the interventions. Fourth, as a consequence of the COVID-19 pandemic, the mode of delivery of the FOCUS+ intervention can differ between dyads, i.e. either face-to-face or via an online video platform. By recording the mode of delivery of the FOCUS+ intervention for each dyad in each country, within-group variations in effectiveness can be monitored.

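### The per-protocol analysis named as the sensitivity analysis excludes every dyad without T1 data, so it cannot test the imputation assumption, although about 35% loss is anticipated

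*Protocol article*

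**What the plan says.** Under Quantitative analysis, the protocol article makes intention-to-treat the primary principle: "All randomized dyads will be included in the mixed model", and "Multiple imputations will be applied". The listed imputation predictors are the baseline score, randomization group, age and further variables such as illness severity. No missingness assumption is named.

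The same paragraph then fixes the second analysis: "The secondary principle is the per-protocol analysis that functions as a sensitivity analysis". Its population is "dyads who have completed all sessions of the FOCUS+ or iFOCUS intervention (except for dyads in the control group) and T1 measurement". The section applies the same two principles to the secondary endpoints and to T2.

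The Sample size calculation section gives the expected loss: "Anticipating a 65% retention rate at T1". It describes this figure as more conservative than earlier studies of the original programme. The Discussion adds that the long questionnaires "may cause a considerable burden and can lead to high nonresponse".

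The other robustness and exploratory analyses serve different purposes. One compares quality-of-life measures within the economic evaluation. The rest are dyad-level, subgroup and country models. None addresses missing T1 scores.

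**The concern.** A sensitivity analysis should vary the assumption on which the primary result most depends. Here that is the model for T1 scores that were never observed. Imputing from observed predictors, with randomization group among them, by default treats non-returners as resembling returners with the same predictors. Active-arm non-returners are then credited with the benefit seen in active-arm returners.

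The per-protocol analysis does not vary that assumption. It removes the people to whom it applies and asks a different question, about dyads who completed treatment and assessment. It also selects unevenly: active-arm dyads must have completed all sessions, while control dyads need only T1. If dyads who are struggling stop attending, both analyses could lean towards the intervention: imputation because non-returners receive returner-like scores, per-protocol because strugglers leave the active arms. Agreement between the two would then give no assurance about the missing data.

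The population makes this more than a formality. Patients have advanced cancer, with an expected survival that may be as short as three months at entry. Allocation is open and the outcomes are self-reported.

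**Working it through.** **Inputs from the article** (Sample size calculation): effect 0.375 SD, alpha 0.0125, power 0.90, 203 evaluable per arm (609 in all), 65% retention, 938 dyads enrolled (313 per group), reference SD 23.8 for emotional functioning in cancer patients. Two-sided testing is stated under the secondary endpoints, and the sample size reproduces only as two-sided (one-sided gives 177 per arm).

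**Reproducing the plan's figures**
- n per arm = 2 × (2.4977 + 1.2816)² / 0.375² = 203.1, which is 204 rounded up, against 203 stated. Power at 203 is 0.8998.
- Enrolment: 203 / 0.65 = 312.3, so 313 per arm. 609 / 0.65 = 936.9, so 937 against 938 stated.
- Planned loss: 1 − 0.65 = 35%. That is 938 − 609 = 329 dyads, or about 110 per arm.

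**Reach of the per-protocol set.** It can hold at most about 65% of dyads, and fewer in the active arms because of the session requirement. By definition it holds none of the roughly 329 dyads without T1.

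**How much the assumption matters.** Illustrative assumptions: 35% missing in each arm, information equal to 203 per arm, no extra variance from imputation, and every active-arm non-returner shifted down by δ from the imputed value with control unchanged.
- SE = √(2/203) = 0.0993 SD.
- Smallest significant difference = 2.4977 × 0.0993 = 0.248 SD (5.9 points at SD 23.8).
- Effect after the shift = 0.375 − 0.35 × δ.
- Tipping shift: δ = (0.375 − 0.248) / 0.35 = 0.36 SD (8.6 points).
- With an assumed baseline correlation of 0.5: SE = 0.0993 × √(1 − 0.25) = 0.0860; critical difference = 0.215 SD; δ = (0.375 − 0.215) / 0.35 = 0.46 SD.

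**Range over the missing share m** (no baseline adjustment, information held at 203 per arm). The last two columns take active-arm non-returners to have no benefit, so the expected effect is 0.375 × (1 − m).

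| m | Tipping shift, SD (points) | Effect if non-returners have no benefit, SD | Power |
|---|---|---|---|
| 20% | 0.64 (15.1) | 0.300 | 70% |
| 25% | 0.51 (12.1) | 0.281 | 63% |
| 35% | 0.36 (8.6) | 0.244 | 48% |
| 45% | 0.28 (6.7) | 0.206 | 34% |

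**Deaths.** The shift above applies to all non-returners. If deaths are not shifted, the tipping value rises. Were 10 of the 35 percentage points deaths (an assumption), it would be 0.127 / 0.25 = 0.51 SD.

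**The case against.** The strongest objection is that this is a condensed article. Tipping-point and control-based imputation normally sit in the statistical analysis plan, which is not shown. A reader might infer that the missing-data assumption is never checked. The documents do not support that: silence in an article does not show that no check is planned. What stands is narrower. The article itself assigns the sensitivity role, and the analysis it chose cannot fill it for missing data.

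A second objection is that the sentence only contrasts two analysis sets, calls per-protocol one sensitivity analysis rather than the only one, and never claims that it tests the imputation. That is fair as a reading, and per-protocol is a conventional companion to intention-to-treat. But no other analysis of the primary outcomes is given that role in the article.

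Three further readings go too far.
- Missing-at-random is the usual default of the imputation described, but the article does not state it. The predictors include illness severity, so the model is not limited to the baseline score.
- The 35% is a deliberately cautious, dyad-level planning figure, not a known share of imputed scores. Bereaved participants may complete an abbreviated package that can include emotional functioning, so caregiver loss may be lower. A data collector at T1 and retention gifts also work against loss.
- Inflated type I error from unequal loss cannot be claimed. The questionnaire burden noted in the Discussion falls on all arms, and no arm-specific retention is given. With equal loss and an equal shift in all arms the bias is zero. An assumed 60% against 70% retention, with non-returners 0.5 SD below imputed values, would give 0.5 × (0.40 − 0.30) = 0.05 SD of bias and an actual level of 2.4% to 2.9% against 1.25%. The 10-point gap is invented for illustration.

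**Conclusion.** The point holds in limited form. The analysis that the article designates as a sensitivity analysis excludes every dyad without T1 and conditions on session completion in the active arms only. It cannot test the assumption behind the multiple imputation, although about 35% dyad-level loss is anticipated. Whether the unseen statistical analysis plan adds such a check is unknown.

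The dependence is large enough to matter. At the planned effect and planned loss, the shift that removes significance (0.36 SD) is slightly smaller than the effect itself (0.375 SD). It becomes 0.46 SD with a baseline correlation of 0.5, and it is larger with less missing data or if deaths are left unshifted. These figures rest on a one-arm shift and on information equal to 203 per arm. The values in points apply to patients only, because the SD of 23.8 is a patient reference value. They do not predict that the result will tip. The change is advisable rather than essential: no figure in the plan is wrong, and the remedy is cheap.

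**What to change.** State a missing-data sensitivity analysis for the primary outcomes, run separately for patients and caregivers:
- Delta-adjusted imputation: for participants alive without T1, lower the imputed active-arm scores in steps (for example from 0 to 0.6 SD, further if needed) and report the shift at which each primary conclusion changes.
- Control-based imputation: impute active-arm non-returners from the control-arm model.
- Report T1 loss by arm and by participant type, with deaths counted separately, so that a reader can judge whether the tipping shift is plausible.

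Keep the per-protocol analysis, but describe it as an adherence analysis. If the statistical analysis plan already contains these runs, only the article's description needs correcting.

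Cost: a few extra imputation runs and one table. No new data and no change to sample size or conduct.

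### The per-protocol sensitivity analysis sets all-session completers against controls not selected on adherence, and the article gives two competing adherence definitions

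*Protocol article*

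**What the plan says.** Under Quantitative analysis, the article makes intention-to-treat primary ("The primary principle is intention-to-treat"), includes all randomized dyads and applies multiple imputation. It then adds: "The secondary principle is the per-protocol analysis that functions as a sensitivity analysis". The population for that analysis is "dyads who have completed all sessions of the FOCUS+ or iFOCUS intervention (except for dyads in the control group) and T1 measurement".

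The outcome model contains randomization group, the baseline value of the outcome and recruitment centre as a random effect. On confounding, the article says: "By including the baseline measurement as a predictor variable (ANCOVA), preexisting differences will be controlled for". The per-protocol analysis is repeated for the secondary endpoints ("We will perform analyses on both ‘intention-to-treat’ and per-protocol principles, applying the same principles as described above"), and the T2 analyses follow the same procedures.

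Later in the same section, under other analyses, the process evaluation is to use "quantitative data from the intervention checklist and routine monitoring to describe adherence to the implementation", and the article continues: "This analysis will determine cut-off points for good intervention adherence and, hence, inform the per-protocol analyses". The Discussion repeats that sentence. The Blinding section says that those analysing the data "will remain blind as to what trial arm dyads were randomized to until the end of the last data-collection point".

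**The concern.** Completing every session happens after randomization, can be observed only in the active arms, and plausibly depends on how the patient's illness develops between T0 and T1. Illness also drives emotional functioning at T1. Filtering only the active arms on it breaks the randomized comparison. The baseline covariate captures the state at T0, not deterioration afterwards.

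A sensitivity analysis is meant to show whether the main result survives different assumptions. If this one can differ from zero when the intervention does nothing, agreement with intention-to-treat is weak reassurance, and a larger per-protocol effect could be misread as the benefit of full participation.

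The second problem is definitional. A fixed all-sessions rule and a cut-off taken from the trial's own adherence data cannot both define the population, and the article does not rank them or say when the choice is made.

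**Working it through.** **The plan's own figures.** Inputs from the sample size section: difference 0.375 SD, alpha 0.05/4 = 0.0125, power 0.90; tests are two-sided (Quantitative analysis). Per arm, n = 2 × ((z for 1 − 0.0125/2 + z for 0.90)/0.375)² = 203.1. The article states 203, which has power 0.8998. At 65% retention, 203/0.65 = 312.3, so 313 per group, as stated. These figures do not depend on the per-protocol analysis. The article gives no session-completion rate and no size for the per-protocol population.

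**Who is filtered on what**

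| Arm | All sessions required | T1 required |
|---|---|---|
| FOCUS+ | yes (3 sessions) | yes |
| iFOCUS | yes (4 sessions) | yes |
| Control | no | yes |

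**Illustrative size of the bias when the true effect is zero.** Assumptions, none from the documents:
- c = share of T1-observed intervention dyads who complete all sessions, 0.6 to 0.9.
- Completion is threshold selection on a latent trait that has correlation r with the T1 residual.
- ρ = correlation between baseline and T1, 0.5 to 0.7.

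Bias in SD units = r × φ(t)/c × √(1 − ρ²), where t is the standard normal quantile at 1 − c and φ is the normal density.

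Example with c = 0.8, r = 0.2, ρ = 0.5: t = −0.842, φ(t) = 0.280, φ(t)/c = 0.350; bias = 0.2 × 0.350 × 0.866 = 0.061 SD.

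The standard error uses 203 controls and 203 × c intervention dyads: √((1 − ρ²)(1/203 + 1/(203c))). The factor √(1 − ρ²) cancels in bias/SE, so the chance of a false significant result does not depend on ρ. With no bias, the chance of a significant result favouring the intervention is 0.0125/2 = 0.00625.

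| c | r | Bias, ρ = 0.5 (SD) | Bias, ρ = 0.7 (SD) | Chance of false significance favouring intervention |
|---|---|---|---|---|
| 0.9 | 0.1 | 0.017 | 0.014 | 0.011 |
| 0.8 | 0.2 | 0.061 | 0.050 | 0.033 |
| 0.7 | 0.2 | 0.086 | 0.071 | 0.056 |
| 0.6 | 0.3 | 0.167 | 0.138 | 0.21 |
| 0.9 | −0.1 | −0.017 | −0.014 | 0.004 |
| 0.6 | −0.1 | −0.056 | −0.046 | 0.001 |

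For positive r the range is 0.014 to 0.167 SD. That is 4% to 45% of 0.375 SD, or 0.3 to 4.0 points at the article's SD of 23.8. With negative r (dyads doing well skip sessions) the sign reverses.

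**Cross-check.** The completer mean minus the arm mean equals (1 − c) × gap, where the gap is how much worse non-completers do after baseline adjustment. The central case (c = 0.8, bias 0.050 to 0.061) implies a gap of 0.050/0.2 = 0.25 to 0.061/0.2 = 0.30 SD.

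**The two definitions side by side.** The definition of the per-protocol population requires all sessions. The process-evaluation text, and its repetition in the Discussion, has cut-offs determined later from checklist and monitoring data. A cut-off other than all sessions gives a different population, and no sentence links the two rules.

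**The case against.** The strongest reply is that little hangs on this. Intention-to-treat is primary, per-protocol is secondary, and no alpha, sample size or success criterion uses it. That stands: the primary inference is not weakened, although a reader might infer otherwise.

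A reader might also take the controls to be unselected. They are not. The T1 requirement applies to every arm, and T1 falls at or after the end of the 12-week intervention period, so dyads lost to death or severe decline before T1 leave the control group too. Only the adherence filter is one-sided.

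A reader might infer that bias toward the interventions is established. The article reports no completion rate and no link between completion and outcome. It also foresees non-clinical reasons for missed web sessions, such as onboarding problems and early exit. The direction is a reasonable expectation in a population for which the plan already lowers expected retention because of advanced disease; it is not a documented fact.

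Finally, a reader might infer that the cut-off will be chosen with outcomes by arm in view, or that it adds bias of its own. The article names adherence data only, not outcomes, as its source, and the Allocation section bars analysis staff from allocation information. A looser cut-off could even lessen the selection. What remains is unresolved flexibility: stated blinding ends at the last data collection, and no locking time is given.

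A condensed article may leave the timing to an analysis plan not shown here. That does not remove a conflict between two rules that the article itself prints.

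**Conclusion.** The point holds in a limited form. The per-protocol contrast is a non-randomized comparison, because completion of all sessions is required in the active arms and has no counterpart in controls; the stated covariates do not correct for this. It probably favours the interventions, by about 0.01 to 0.17 SD under a null effect and about 0.05 to 0.06 SD in the central case. Those figures rest on assumed completion of 60% to 90%, an assumed prognostic correlation of 0.1 to 0.3, and 203 T1-observed dyads per arm as planned. Separately, the adherence definition is stated in two ways that need reconciling. The consequence is confined to how the per-protocol results are read, for the primary endpoints and wherever the same procedure is repeated.

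**What to change.** 1. Reconcile the per-protocol definition, the process-evaluation text and the Discussion into one adherence definition, dated and locked before anyone setting it sees outcomes by arm.

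2. Describe the per-protocol result as a non-randomized, supportive comparison, not as a check on the robustness of intention-to-treat.

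3. For the effect of receiving the intervention, add or substitute an instrumental-variable estimate for each active arm versus control, with randomization as the instrument and the same baseline covariate, centre and multiple imputation. The exposure should be number of sessions completed or any session received. A binary all-sessions exposure would assume that partial attenders gain nothing, although they too receive content, so it would breach the exclusion restriction.

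The cost is wording and one further model per comparison; Table 4 already plans session data for both active arms. The downsides should be stated: a wider interval, a linear-dose assumption (session count) or an exclusion assumption (any session), and a null test that adds little to intention-to-treat. The estimate is roughly the intention-to-treat effect divided by the share exposed (for example, 1/0.8 = 1.25 times at 80%), so it will also exceed a positive intention-to-treat effect when exposure is incomplete. It answers a different question and is not independent confirmation.
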